## Abstract

**Background:**

Although most patients with low back pain (LBP) recover within a few weeks a significant proportion has recurrent episodes or will develop chronic low back pain. Several mainly psychosocial risk factors for developing chronic LBP have been identified. However, effects of preventive interventions aiming at behavioural risk factors and unfavourable cognitions have yielded inconsistent results. Risk tailored interventions may provide a cost efficient and effective means to take systematic account of the individual risk factors but evidence is lacking.

**Methods/Design:**

This study will be a cluster-randomised controlled trial comparing screening and a subsequent risk tailored intervention for patients with low back pain to prevent chronic low back pain compared to treatment as usual in primary care. A total of 600 patients from 20 practices in each study arm will be recruited in Berlin and Goettingen. The intervention comprises the following elements: Patients will be assigned to one of four risk groups based on a screening questionnaire. Subsequently they receive an educational intervention including information and counselling tailored to the risk group. A telephone/email consulting service for back pain related problems are offered independent of risk group assignment. The primary outcomes will be functional capacity and sick leave.

**Discussion:**

This trial will evaluate the effectiveness of screening for risk factors for chronic low back pain followed by a risk tailored intervention to prevent chronic low back pain. This trial will contribute new evidence regarding the flexible use of individual physical and psychosocial risk factors in general practice.

**Trial registration:**

ISRCTN 68205910

## Background

Low back pain (LBP) is an epidemiologically and economically important health problem [1-4]. An underlying specific pathology cannot be identified in most patients consulting in primary care and about 90% of all low back problems are therefore considered as being of non-specific origin [5]. Although it is expected that patients seen in primary care will recover within a few weeks a substantial proportion continues to suffer from LBP [6,7]. Therefore it is of high relevance to recognize patient characteristics predictive of a chronic or recurrent course of low back pain at an early stage [8]. Accordingly, a wide range of risk factors have been associated with the development and persistence of low back pain including life style factors, previous pain symptoms, psychosocial factors, work place factors, and sociodemographic as well as socioeconomic variables [9]. Among these, two sets of risk factors have demonstrated a particular importance in predicting the course of low back pain. Previous pain episodes [10-12], and psychosocial risk factors such as depression, and fear-avoidance beliefs [13,14].

Recent studies indicate that brief self-rating questionnaire based risk factor assessments may predict the course of low back pain and major related outcomes like sick leave [15-17]. Implementing a screening questionnaire might improve risk factor assessments in ambulatory settings. However, uncertainty remains how to translate the results of risk factor assessments into therapeutic action under field conditions. This concerns individual benefits as well as cost-effectiveness.

As could be demonstrated, educational interventions may be effective, in particular with regard to patients with acute or subacute back pain [18]. However, a brief provision of back pain related information may not be enough to substantially improve main indicators of disability such as sick leave [19]. Accordingly, there is no related recommendation in existing guidelines [20]. Information should rather be complemented with concrete cognitive-behavioural interventions [21,22].

While the European Guidelines on the treatment of acute back pain [20] conclude that scientific evidence does not support exercise therapy in patients with acute back pain they do agree on the benefits of the advice to stay active. Activating interventions may rather exert beneficial effects through an implicit change of adverse cognitions like fear-avoidance beliefs [23,24]. They may be more effective in patients with moderate disability and fear avoidance levels [25].

Content and extent of interventions should not be independent of the individual risk factors [25-27]. This may also be a reason for the limited effectiveness of recent trials on psychosocial interventions for back pain in primary care [28,29]. While risk tailored interventions have repeatedly been researched in other health related domains like smoking or hypertension [30-33] limited evidence is available with regard to pain problems, despite the repeated focus on subgroups [15,34,35]. Two studies evidenced the strength of tailored interventions with regard to musculoskeletal pain, and to a lesser degree temporomandibular disorders [36,37]. However there is a lack of evidence with regard to low back pain, in particular in combination with a screening tool that is easily implemented in general practice. Therefore we designed this randomized controlled trial to assess the effectiveness of a risk tailored-intervention program based on a brief risk screening. The study will be conducted in a primary care setting because this seemed most appropriate to target back pain patients at an early stage in the course of their illness.

## Methods/Design

### Aims

The aim of this study is to assess the effectiveness of a brief risk factor screening followed by a risk tailored intervention for patients consulting for acute to subacute low back pain in primary care. Key outcomes comprise functional capacity, sick leave, self-management activities, negative pain-related cognitions and a reduced utilization of health care services. Furthermore we aim to assess the acceptance of a short risk tailored-intervention among patients with acute and subacute low back pain and the utilization of an additional E-mail or telephone service.

### Design

The study is a two-armed cluster-randomized controlled study. General practices will be assigned at random to the control or intervention arm of the study and subsequently recruit patients. This cluster randomization approach is frequently used in ambulatory settings because of its high degree of internal validity and for pragmatic reasons[38]. Twenty GPs shall participate in each study region of whom half will be assigned to the control or the intervention group. Each GP should recruit 30 patients. This will lead to a total of 1200 patients with 600 belonging to the intervention, and 600 to the control arm of the study, respectively. Back pain and related variables will be recorded at baseline and after 6 and 12 months as outlined in Figure 1.

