#### Patients

Consecutive patients consulting for low back pain in general practices will be invited to participate in the study. Practice nurses will perform a first screening for eligibility based on non-medical criteria. Patients will receive an information leaflet regarding the purpose and content of the study. Patients willing to participate complete the consent form. A list of inclusion and exclusion criteria is given in Table 1. Should any of the exclusion criteria be recognized during the subsequent consultation, the patient will be informed by the doctor and excluded from the study.

**Table 1 T1:** Inclusion and exclusion criteria

Inclusion criteria	• consulting for low back pain
	• age 20 to 60 years
	• German language proficiency
	• ability to give informed consent
Exclusion criteria	• treatment for the present low back pain episode for more than 3 months
	• severe co-morbidity (cardiovascular, metabolic, inflammatory disease or tumors)
	• back pain of specific origin, e.g. ankylosing spondylitis
	• prior spine surgery
	• specialized pain treatment or rehabilitation for low back pain within the last 5 years
	• ongoing early retirement or pension claim
	• poor general condition
	• severe pain during night or rest
	• signs of radiculopathy like numbness, muscle weakness, loss of reflexes

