### Randomization

The randomization of GPs to the intervention or control arm will be conducted externally by the coordinating centre of the study in Greifswald. GPs consenting to participate are reported by the two regional coordinators to the study centre. The subsequent randomization will be conducted blockwise with blocks of four, six, and eight units length, to veil the possible allocation of the next GP.

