#### Risk screening

After giving their informed and written consent to participate in the study patients will receive a brief self-rating risk screening inventory concerning yellow flags that are predictive of chronic back pain. The screening items are based on a German translation of the Örebro Musculoskeletal Pain Screening Questionnaire [41,42]. Ten out of the 25 items comprised by the instrument were selected for our investigation: pain intensity in the past week (one item), fear-avoidance beliefs (two items), depressive mood (two items), functional ability (four items), and body locations of pain (one item). The selection of these items was mainly based on previous findings concerning predictors for the course of back pain as outlined in the introduction. A brief instrument based on the selected domains was useful in predicting disability [15] and provided the conceptual background for our risk groups as described below.

The completed questionnaires will be returned to the practice nurse prior to the consultation and immediately analyzed to be available during consultation only in the intervention arm. Based on their screening responses patients in the intervention arm will be assigned to one of four risk groups (low/only physical/only psychological/physical and psychological). The low risk group comprises subjects without strong pain symptoms (defined by high intensity low back pain with functional limitations or multilocated pain) as well as low levels of depression and fear avoidance. The physical risk group comprises subjects with severe low back pain. Subjects that belong to this group experience high intensity and disabling back pain as well as pain in different body locations. The psychological risk group comprises subjects with strong low back pain and high levels of depression and fear avoidance. Subjects may be assigned to either one or both risk groups.

Apart from the subsequently described risk tailored intervention all patients receive treatment as usual. A national guideline for management of low back pain in primary care was published in 2001 [20].

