### Assessing Selection Bias

Non-response bias may threaten the validity of our results. Therefore all practices will document successful and failed recruitment attempts. Age and sex of patients who refuse to participate will be recorded. Drop-out to the follow up surveys will be statistically controlled based on the participants' responses at baseline as described in data analysis.

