### Data analysis

Baseline and follow up data will be presented using common parametric and non-parametric descriptive statistics. In addition to cross-sectional analysis to compare the control and intervention group at the second and last follow up, longitudinal analysis will use multilevel regression and generalized estimation equating (GEE) models with the outcome variables as outlined above. Non-response and drop out will primarily be accounted for by calculating statistical weights, or by conducting complete case analysis under the missing at random assumption, as appropriate. Comparisons predominantly concern the entire intervention group vs. the control group. A time vs. treatment group interaction will be computed to assess the benefits of the brief risk tailored assessment vs. treatment as usual.

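### Allocated practices recruit their own patients, the protocol commits to no between-arm check of enrolment, and neither 12-month analysis as worded would remove a baseline gap

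*Protocol article*

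**What the plan says.** **Order of events.** The protocol article, Design: "General practices will be assigned at random to the control or intervention arm of the study and subsequently recruit patients". Under Patients, those consulting for low back pain are to be invited consecutively. "Practice nurses will perform a first screening for eligibility based on non-medical criteria". Before consent, "Patients will receive an information leaflet regarding the purpose and content of the study".

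**Concealment.** Under Randomization, allocation is done externally in blocks of varying length "to veil the possible allocation of the next GP". This protects the assignment of practices. It says nothing about the enrolment of patients once a practice has its arm.

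**Check on selection.** Under Assessing Selection Bias, the threat is described as non-response. Practices log their recruitment attempts, whether or not these succeed, and "Age and sex of patients who refuse to participate will be recorded". Baseline responses are assigned to the control of drop-out.

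**Data in both arms.** Back pain and related variables are recorded at baseline (Design), and control patients also complete the risk screening before the consultation (Control group).

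**Analysis.** Data analysis plans a "cross-sectional analysis to compare the control and intervention group at the second and last follow up", multilevel and GEE longitudinal models, and a time-by-group interaction to judge benefit.

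**The concern.** The Design section credits cluster randomisation with strong internal validity. That holds for the comparison of practices. It carries over to patients only if enrolment does not depend on arm. An intervention practice processes the screening result, gives tailored advice and can offer courses and a counselling line, whereas a control practice offers usual care and questionnaires. Staff who know this may recruit differently, and patients with more pain or distress may have more reason to agree where help is on offer. The arms could then differ at baseline in the factors that the Background names as the main predictors of course: earlier pain episodes, depression and fear-avoidance.

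Age and sex of refusers say little about selection on those factors. Data analysis mentions weights for non-response and drop-out. If these are meant to reach people who never enrolled, they can use only what is recorded on them. At stake is whether a 12-month difference in function or sick leave can be attributed to the intervention. A larger sample would not reduce this bias.

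**Working it through.** **1. The plan's own figure.** Inputs from Design: d = 0.3, 5% significance, 80% power, ICC 0.025, final cluster size 20.
- Unclustered n per arm = 2 × (1.96 + 0.8416)² / 0.3² = 174.4, so 175.
- Design effect = 1 + (20 − 1) × 0.025 = 1.475, which the protocol rounds to 1.5.
- 175 × 1.475 = 258.1 (259) and 175 × 1.5 = 262.5 (263). A t-based n of 175.4 × 1.5 = 263.1 (264).

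The stated 265 per arm is reproduced closely, so the sample size is not in question.

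**2. Precision at 12 months.** With one third lost, 600 × 2/3 = 400 completers per arm, 20 per practice. Effective n = 400 / 1.475 = 271.2. SE = √(2 / 271.2) = 0.0859 SD.

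**3. Bias from a baseline gap.** Let s be the gap between arms in baseline function, in SD, and r the correlation between baseline and 12 months. Assume equal SDs, a linear relation and no true effect.
- Follow-up values compared without baseline adjustment: bias = r·s.
- Change from baseline (time by group): bias = r·s − s = −(1 − r)·s.
- Follow-up adjusted for the baseline value: r·s − r·s = 0, for the part carried by that variable.

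The first two always have opposite signs. If intervention practices enrol worse cases, the follow-up comparison is biased against the intervention and the change contrast in its favour.

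**4. Size.** The documents give neither s nor r, so both are assumptions, shown over a range. Rejection rate with no true effect = P(Z > 1.96 − b/SE) + P(Z < −1.96 − b/SE), where b is the bias. For the change contrast the SE is multiplied by √(2(1 − r)), using the same design effect, so those rates are approximate. Ranges are given in the order r = 0.4 to r = 0.7.

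| Gap s | Follow-up bias (SD) | Error rate | Change bias (SD, absolute) | Error rate |
|---|---|---|---|---|
| 0.1 | 0.04 to 0.07 | 8% to 13% | 0.06 to 0.03 | 10% to 7% |
| 0.2 | 0.08 to 0.14 | 15% to 37% | 0.12 to 0.06 | 25% to 15% |
| 0.3 | 0.12 to 0.21 | 29% to 69% | 0.18 to 0.09 | 48% to 27% |

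At r = 0.5 and s = 0.2 the biases are +0.10 and −0.10 SD. For s = 0.2 the follow-up bias is 0.08/0.3 = 27% to 0.14/0.3 = 47% of the planned effect. If the worse cases are in the intervention arm, power of the follow-up comparison at d = 0.3 falls from 94% to between 73% and 46%. The change contrast moves the other way.

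**5. Sensitivity to drop-out.** With 40% lost there are 360 completers per arm, 18 per practice: design effect 1.425, SE 0.0890. For s = 0.2 the error rates are 15% to 35% (follow-up) and 23% to 14% (change), so the picture is the same.

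**6. A related route, not in these figures.** Exclusion can also follow consent: "Should any of the exclusion criteria be recognized during the subsequent consultation, the patient will be informed by the doctor and excluded from the study". At that consultation the screening result is "immediately analyzed to be available during consultation only in the intervention arm", so this later step is not blind to arm either.

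Nothing was computed for sick leave. The documents give no distribution for it, and results on the SD scale do not transfer directly to days.

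**The case against.** Several points on the other side stand.

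- **Safeguards exist.** Invitation is to be consecutive, and the nurse's first screen uses non-medical criteria. Both limit discretion over whom to approach. Neither controls who agrees, and the article describes no recruiter blind to arm and no identification of patients before randomisation.
- **A reader might infer that the bias would go unseen.** The documents do not support this. Attempts are logged, and baseline and screening data are collected in both arms, so differing acceptance and measured imbalance among enrolled patients could be seen. What is absent is a commitment to compare the arms on them. Only imbalance in unmeasured factors would stay hidden.
- **A reader might infer that the 12-month comparison is planned as unadjusted.** The article is only silent on covariates, and a list may stand in an analysis plan that is not shown. The time-by-group contrast also uses the baseline value, although it does not remove the bias.
- **A reader might infer that the leaflet reveals the arm.** The article does not say whether it differs between arms or discloses allocation. The point does not need this.
- **Knowledge of arm is inferred.** It is not stated outright, but practices that deliver the intervention can hardly be unaware of it.
- **The sizes are hypothetical.** No figure in the documents says that a gap will arise or how large it would be.

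**Conclusion.** The point holds as a design risk with an incomplete safeguard. It does not show that bias will occur. Enrolment follows allocation in practices that know their arm, the dedicated selection section addresses non-response without committing to a comparison of arms, and the two analyses as worded respond to a baseline gap in opposite directions. Under selection they could disagree, and the article gives no rule for resolving that.

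For a 0.2 SD gap the distortion is 0.08-0.14 SD in the follow-up comparison and 0.06-0.12 SD in the change contrast, against a planned effect of 0.3 SD. The nominal 5% error becomes roughly 15-37% and 15-25%. These figures rest on the assumed gap, an assumed correlation of 0.4-0.7, 400 completers per arm and the protocol's ICC of 0.025. Even if an unseen analysis plan lists covariates, naming baseline adjustment here is worthwhile: it removes the measured part of any gap and improves precision.

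**What to change.** **Data analysis.** Make the primary 12-month comparison of functional ability a cluster-aware model (multilevel or GEE) adjusted for baseline functional ability, the pre-consultation screening score, age and sex. Use the same covariates for sick leave, in a model suited to that outcome. The screening score is completed before the consultation in both arms, so the intervention cannot have affected it.

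**Assessing Selection Bias.** Add a comparison by arm of the proportion consenting, from the recruitment log, and of the baseline screening profile of enrolled patients. State that a clear imbalance will be reported as a limit on the causal claim.

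**Cost.** Wording only, since the log and all these variables are already planned. As a rough guide to the gain, adjusting for baseline function multiplies the SE by about √(1 − r²), which is 0.92 at r = 0.4 and 0.71 at r = 0.7, if the design effect is unchanged. The limitation is that adjustment removes only imbalance in measured factors, so the by-arm comparison is needed as well.

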**Figure 1 F1:**
[figure not shown]
**Back pain and related variables recorded at baseline and after 6 and 12 months**.

This sample size is based on a power analysis that accounted for an assumed drop-out of one third of the initial participants to the second follow up as well as for a loss of power due to correlated data within primary sampling units. Based on previous results in a GP intervention study [39], an intraclass-correlation of 0.025 is a plausible assumption for the target outcomes of our study. Given a final cluster size of on average 20 subjects the design effect will be approximately 1.5. To detect a difference in functional disability between intervention and control group at the second follow-up that corresponds to a Cohen's d effect size of 0.3 with a significance level of 5%, and a power of 80%, a final sample of 265 subjects in each study arm will be necessary. Assuming a total drop out rate of even 40% till the second and last follow up, the initial sample size of 600 subjects per study arm will suffice to detect the outlined effect.

### Study population and recruitment

#### General practitioners

General Practitioners (GPs) in Göttingen and vicinity and Berlin are invited to take part in the trial by letter. Addresses are obtained from the local health boards. In case of non-response to the letter GPs are contacted by telephone or personally. From previous experience it is known that roughly 15-20% agree to participate [40].

#### Patients

Consecutive patients consulting for low back pain in general practices will be invited to participate in the study. Practice nurses will perform a first screening for eligibility based on non-medical criteria. Patients will receive an information leaflet regarding the purpose and content of the study. Patients willing to participate complete the consent form. A list of inclusion and exclusion criteria is given in Table 1. Should any of the exclusion criteria be recognized during the subsequent consultation, the patient will be informed by the doctor and excluded from the study.

**Table 1 T1:** Inclusion and exclusion criteria

Inclusion criteria	• consulting for low back pain
	• age 20 to 60 years
	• German language proficiency
	• ability to give informed consent
Exclusion criteria	• treatment for the present low back pain episode for more than 3 months
	• severe co-morbidity (cardiovascular, metabolic, inflammatory disease or tumors)
	• back pain of specific origin, e.g. ankylosing spondylitis
	• prior spine surgery
	• specialized pain treatment or rehabilitation for low back pain within the last 5 years
	• ongoing early retirement or pension claim
	• poor general condition
	• severe pain during night or rest
	• signs of radiculopathy like numbness, muscle weakness, loss of reflexes

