### Control group

Control patients will receive treatment as usual. They participate in the accompanying survey, including the baseline assessment, and the two follow-up surveys at six and twelve months. Furthermore, control patients complete the risk screening prior to their consultation. However, results of this screening will not be communicated to the doctor nor to the patient. Because control patients are recruited in different practices from intervention patients there is a low risk of cross-contamination.

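### Doctors apply the medical exclusions after randomisation and consent, in a consultation where only the intervention arm has the scored risk result, so post-consent exclusions can differ by arm in either direction

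*Protocol article*

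**What the plan says.** The article gives the order of events across several sections.

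1. Design: "General practices will be assigned at random to the control or intervention arm of the study and subsequently recruit patients".
2. Patients: "Practice nurses will perform a first screening for eligibility based on non-medical criteria". The medical criteria are therefore left to the doctor.
3. Patients: "Patients willing to participate complete the consent form". This comes before the consultation.
4. Risk screening: "After giving their informed and written consent to participate in the study patients will receive a brief self-rating risk screening inventory". It covers pain intensity, functional ability, pain locations, depressive mood and fear-avoidance. The nurse collects it before the consultation and it is "immediately analyzed to be available during consultation only in the intervention arm".
5. Control group: patients complete the same screening, but "results of this screening will not be communicated to the doctor nor to the patient".
6. Patients: "Should any of the exclusion criteria be recognized during the subsequent consultation, the patient will be informed by the doctor and excluded".

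On selection, the section Assessing Selection Bias has all practices document successful and failed recruitment attempts. It adds "Age and sex of patients who refuse to participate will be recorded" and promises statistical control of drop-out to the follow-up surveys. Data analysis plans weights or complete-case analysis for non-response and drop-out, a cross-sectional comparison at the last follow-up, and longitudinal models with a time-by-treatment interaction.

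**The concern.** Randomising practices balances the patients who come to them. It does not protect against filtering that happens afterwards and may depend on arm. Here the last filter is applied by a doctor who knows the arm, because intervention doctors deliver part of the intervention. In one arm only, that doctor also has a prognostic score available. The score's content is close to the primary outcome of functional disability.

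A doctor who sees a high-risk result might probe further and exclude more patients, or might keep a borderline patient in so that the groups can be offered. Either would make the analysed arms differ in prognosis for reasons unrelated to treatment. A larger sample would not cure this. A consented patient whom the doctor then excludes is neither a refuser nor a drop-out from follow-up, and those are the only two groups the selection-bias provisions name.

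**Working it through.** **Step 1. Is the asymmetry in the text?** Set side by side:

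| Step | Intervention arm | Control arm |
|---|---|---|
| Practice allocated before recruitment | yes | yes |
| Consent before the consultation | yes | yes |
| Screening completed before the consultation | yes | yes |
| Score available to the doctor at the consultation | yes | no |
| Doctor applies medical exclusions in that consultation | yes | yes |

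The arms differ in one row, and that row bears on the next decision. The article describes no step that fixes eligibility before the score is available.

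**Step 2. Is there room for judgement?** Most Table 1 exclusions are matters of history or examination: treatment duration, prior spine surgery, specific origin, earlier specialised treatment, pension claim, signs of radiculopathy. Severe co-morbidity is qualified by disease groups about which the screening says little. Two remain without a threshold and could be coloured by the screening result: poor general condition, and severe pain at night or at rest.

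**Step 3. Is this a sample-size problem?** Inputs from Design: d = 0.3, 5% level (taken as two-sided), 80% power, ICC 0.025, final cluster size 20.

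- Individually randomised n per arm = 2 × (1.960 + 0.842)² / 0.3² = 174.4, so 175 (176 with the t distribution).
- Design effect = 1 + 19 × 0.025 = 1.475, stated as about 1.5.
- 175 × 1.475 gives 259; 175 × 1.5 gives 263; 176 × 1.5 = 264. The stated 265 is reproduced within 3%.
- With 40% drop-out: 265 / 0.6 = 442 per arm, below the planned 600.

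The plan could lose about 1 − 442/600 = 26% of each arm and keep its power. The issue is bias only.

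**Step 4. How large could the bias be?** The documents give no exclusion rates, so everything in this step is assumed. Suppose one arm excludes an extra share p, all of it from the top of a normally distributed risk measure, and that measure correlates 0.5 with the 12-month outcome. The mean of a standard normal after removing its top share p is −φ(z)/(1 − p), where z is the (1 − p) quantile.

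| p | Shift in risk mean | × 0.5 = shift in outcome | ÷ 0.3 |
|---|---|---|---|
| 5% | −0.1031/0.95 = −0.109 | 0.054 SD | 18% |
| 10% | −0.1755/0.90 = −0.195 | 0.097 SD | 32.5% |

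A second route assumes only that the extra excluded patients are y SD worse on the outcome than their arm's mean. The shift is then p·y/(1 − p). For y = 0.5 to 1.0 this is 0.03 to 0.05 SD at p = 5% and 0.06 to 0.11 SD at p = 10%, the same order of size.

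**Step 5. What does the analysis do to it?** Those figures apply to an unadjusted comparison at 12 months. In a contrast of change from baseline, with equal SDs at both times, the shift becomes (0.5 − r₀) times the shift in risk mean, where r₀ is the correlation of the risk measure with baseline function. For any r₀ between 0 and 1 this is smaller in absolute size than the figures above, though its sign can reverse. Adjustment for baseline function and screening score would also reduce the shift, since it removes the part of the selection that runs through measured values.

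**The case against.** The strongest case on the other side has four parts.

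- **Detection.** A reader might infer that the plan keeps nothing with which to detect such selection. The article does not support that. All practices log failed recruitment attempts, and a consented patient later excluded could reasonably be entered there. Screening and baseline data are collected in both arms, so retained patients can be compared. This part stands. What the article does not state is whether the log covers exclusions after consent, or that these will be compared by arm.
- **Mechanism.** No criterion refers to the screening score, most are factual, and the screening lists no item on night or rest pain. The score is said to be available during the consultation; the article does not say that the doctor reads it before judging eligibility. This narrows the concern to the softer criteria but does not close it, because nothing in the stated order prevents it.
- **Size.** Removing exactly the top-risk tail is an extreme pattern that no criterion prescribes, and the planned time-by-treatment interaction would not carry a baseline difference straight through. Both points stand. The figures are upper-end and illustrative.
- **Brevity.** Exclusion logs and covariate lists are commonly left to the full protocol or analysis plan, so their absence here is not a fault in itself. The point rests on the order of events that the article does describe.

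**Conclusion.** The point holds as a design risk. The article lets doctors decide medical eligibility after randomisation and consent, with a prognostic result available in one arm and withheld in the other, and at least two criteria leave room for judgement. Post-consent exclusions can therefore differ by arm.

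A reader might infer that they will differ, or that the bias favours the intervention. The documents support neither: they give no exclusion rates, and the direction could go either way. The 0.05 to 0.10 SD is not an estimate of the bias. It assumes an extra 5% to 10% excluded in one arm only, all from the highest-risk tail, a 0.5 correlation with outcome, and an unadjusted 12-month comparison. Under baseline adjustment or the planned time-by-treatment contrast it is smaller. Against a target of d = 0.3, even the lower figure is enough to justify an inexpensive safeguard.

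**What to change.** 1. In both arms, have the doctor record the decision on the existing Table 1 exclusions before the scored screening sheet is released. In control practices the form is completed at the same point and no sheet follows. No criterion changes.
2. For every exclusion after consent, keep the reason, the arm and the screening answers already completed. State that the recruitment log covers these cases, and compare exclusion rates and screening scores by arm.
3. Adjust the 12-month comparison for baseline function and screening score, both already collected in both arms.

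**Cost.** One short form and a log entry per exclusion. Some criteria need history or examination, so intervention doctors would see the score somewhat later in the consultation and the practice must manage that handover. The consent wording should allow screening answers of excluded patients to be kept.

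**What remains.** Reordering does not blind the doctor to arm. An intervention doctor who knows the groups are on offer could still apply the softer criteria differently, and adjustment cannot remove selection on unmeasured features. The report should acknowledge this.
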